## Exclusion Criteria

- Age < 18 years
- Diagnosis of low-grade anal dysplasia (AIN 1, LSIL) by HRA
- Known anal, vulvar, cervical, or penile cancer
- CD4 count < 200 at the time of consideration for entry into this study. Patients, whose CD4 counts drop below 200 at any timepoint in this study, will be pulled to the standard of care treatment arm of surgical ablation.
- Unable to provide informed consent
- Currently receiving systemic chemotherapy or radiation therapy for another cancer.
- Patients who are on medical treatment with systemic immunosuppressants or steroids (e.g., active autoimmune disease)
- Extensive anal condyloma precludes the ability for the clinician to visualize HSIL during HRA
- Pregnant female
- Weight < 50 kg.

## Inclusion of Women and Minorities

NIH policy requires that women and members of minority groups and their subpopulations be included in all NIH-supported biomedical and behavioral research projects involving NIH-defined clinical research unless a clear and compelling rationale and justification establishes to the satisfaction of the funding Institute & Center (IC) Director that inclusion is inappropriate with respect to the health of the subjects or the purpose of the research. Exclusion under other circumstances must be designated by the Director, NIH, upon the recommendation of an IC Director based on a compelling rationale and justification. Cost is not an acceptable reason for exclusion except when the study would duplicate data from other sources. Women of childbearing potential should not be routinely excluded from participation in clinical research. Please see <http://grants.nih.gov/grants/funding/phs398/phs398.pdf>.

This clinical trial will not exclude potential subjects from participating in this or any study solely on the basis of ethnic origin or socioeconomic status. Every attempt will be made to enter all eligible patients in this protocol to address the study objectives in a population representative of patients with solid organ tumors treated by any of the participating institutions. (See Planned Enrollment Table in Section 14.4)

# REGISTRATION PROCEDURES

## General Guidelines

Following registration, patients should begin protocol treatment within 4 weeks. Any issues that would cause treatment delays should be discussed with the site Principal Investigator. If a patient does not receive protocol therapy following registration, the patient’s registration on the study may be canceled. The Study Coordinator should be notified of cancellations as soon as possible.

# TREATMENT PLAN

## Agent Administration

Treatment will be administered either on an outpatient basis or remotely, as a telemedicine visit. Reported adverse events and potential risks are described in Section 7. Appropriate dose modifications are described in Section 6. No investigational or commercial agents or therapies other than those described below may be administered with the intent to treat the patient’s disease process.

| **Dose Escalation Design** | | | | |
| --- | --- | --- | --- | --- |
| **Cohort** | **Dose (mg)** | **Number of Treatment Cycles** | **Designated Weeks of Artesunate Administration** | **Number Subjects** |
| **I** | 200 | 2 | 0, 2 | 3 |
| **II** | 200 | 3 | 0, 2, 4 | 3 |
| **III** | 400 | 2 | 0, 2 | 3 |
| **IV** | 400 | 3 | 0, 2, 4 | 3 |
| **V** | 600 | 2 | 0, 2 | 3 |
| **VI** | 600 | 3 | 0, 2, 4 | 3 |

***Note: Each cycle = 5 days

Artesunate suppositories will be administered intra-anally on days 1 to 5, and the dosing schedules will vary between 2 and 3 cycles. A dose-limiting toxicity for the Artesunate suppository is defined as any Grade 2 or greater toxicities in any organ system (or Grade 3 or greater toxicities), as delineated in CTCv4.0. Patients will be continued on treatment until disease progression to cancer, unacceptable toxicity, death, pregnancy, withdrawal of consent, or study termination.

The MTD will be determined utilizing a modified 3 + 3 design. The 3 + 3 dose escalation will consist of 6 dose levels in combination with variation in dosing schedules the single agent Artesunate, with additional de-escalation steps. An expansion cohort of 12 patients will be included at the MTD. Once MTD is found, then secondary outcomes will be evaluated.

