**Cohort IV**:

**400 mg** x 5 daily doses/cycle.

**3 cycles** administered at weeks 0, 2, 4

**De-escalate** to **200 mg** x 5 daily doses/cycle.

**1 cycle** administered at week 0

**De-escalate** to **400 mg** x 5 daily doses/cycle.

**1 cycle** administered at week 0

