## Definition of Dose-Limiting Toxicity

A dose-limiting toxicity (DLT) is defined as any drug-related Grade 2 (moderate; minimal, local, or noninvasive intervention indicated; limiting age appropriate instrumental ADL) or greater drug-related toxicities in any organ system (or Grade 3 or greater toxicities–severe or medically significant but not immediately life-threatening; hospitalization or prolongation of hospitalization indicated; disabling; limiting self care ADL**) in any organ system (including gastrointestinal, dermatologic, and neurologic), as delineated in Common Terminology Criteria for Adverse Events v4.0 (CTCAE).

This above definition of dose-limiting toxicity applies to the drug that is being studied—the artesunate suppository. Post-procedural complications related to the HRA procedure are not dose limiting.

The dose limiting toxicity determining period for the study will extend to 1 week after the last cycle of artesunate suppository. Thus, for the 2 cycles, the DLT determining period will extend to 3 weeks; for 3 cycles, it will extend to 5 weeks.

Beyond the DLT determining period, if patients in a specific cohort have complete resolution of their high-grade dysplastic lesions, then the plan will be to stop at this dosing cycle and frequency and move into the 12-patient expansion cohort.

Management and dose modifications associated with the above adverse events are outlined in Section 6.

Dose escalation will proceed within each cohort according to the modified 3+ 3 design with de-escalation schema and an expansion cohort at MTD. Dose-limiting toxicity (DLT) is defined as above.

The specific details are as follows,

The 3 + 3 dose escalation will consist of 6 dose levels in combination with variation in dosing schedules the single agent Artesunate, with additional de-escalation steps. An expansion cohort of 12 patients will be included at the MTD. Once MTD is found, then secondary outcomes will be evaluated. In MTD expanded patient cohort, anal intraepithelial neoplasia (AIN) regression from AIN 2/3 to low-grade anal intraepithelial neoplasia (AIN 1) or no residual AIN will be assessed through subsequent HRA evaluation. Cytology specimens will be tested through quantitative PCR for HPV viral load during initial and subsequent HRA evaluations. A tissue bank will be created for future studies.

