# STATISTICAL CONSIDERATIONS

## Study Design/Endpoints

The primary objective of this trial is to determine the MTD or recommended Phase 2 dose (RP2D) of Artesunate. The MTD will be determined using a modified 3 + 3 design, in which the MTD is defined as the highest dose level tested at which ≤20% patients experience dose limiting toxicity (DLT). The 3 + 3 dose escalation will consist of 6 dose levels in combination with variation in dosing schedules the single agent Artesunate. In addition, if DLT’s are identified at any dose, there are possible intermediate dose de-escalation steps allowed (i.e. to have only one administration at a particular dose) An expansion cohort will occur at MTD. Once MTD is found, then secondary outcomes will be evaluated. There is a 1-week washout period before advancing to the next Artesunate dose level.

| **Dose Escalation Design** | | | | |
| --- | --- | --- | --- | --- |
| **Cohort** | **Dose (mg)** | **Number of Treatment Cycles** | **Designated Weeks of Artesunate Administration** | **Number of patients** |
| **I** | 200 | 2 | 0, 2 | 3 |
| **II** | 200 | 3 | 0, 2, 4 | 3 |
| **III** | 400 | 2 | 0, 2 | 3 |
| **IV** | 400 | 3 | 0, 2, 4 | 3 |
| **V** | 600 | 2 | 0, 2 | 3 |
| **VI** | 600 | 3 | 0, 2, 4 | 3 |

More specifically:

This is a modified 3 + 3 design. Based on previous studies of rectally administered Artesunate for the treatment of malaria, the safety profile demonstrates a low probability of dose limiting toxicity in children, as well as adults. The first cohort will consist of 3 patients who receive the initial dose of a 200-mg suppository administered in cycles of 5 daily doses at weeks 0 and 2. If none of the three patients in a cohort experiences a dose-limiting toxicity, another three patients will be treated at the next higher dose level. If 1 out of 3 patients experiences dose-limiting toxicity, then the next 3 patients will be treated at the same dose level. If 2 out of 6 patients experience a DLT, then de-escalation to the next lower level will occur. The modification of the 3 + 3 design consists of the extra de-escalation steps as noted on the left of the diagram pictured below.

If any dose has 2 (or more) DLTs then the MTD will be the dose that is below that dose that has 1 or less DLTs out of 6 patients. Once the MTD is identified then additional patients will be added to this cohort to allow a total of 12 patients.

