# APPENDIX A: STUDY CALENDAR

Baseline evaluations are to be conducted within 4 week prior to start of protocol therapy. In the event that the patient’s condition is deteriorating, laboratory evaluations should be performed per they study physician’s discretion within 48 hours prior to initiation of the next cycle of therapy.

| **Surveillance Period** | | | | | | | | |
| --- | --- | --- | --- | --- | --- | --- | --- | --- |
|  | Screen | Cycle 1 (wk 0) | Cycle 2 (wk 2)1 | Cycle 3 (wk 4)1 | Wk 6 | Wk 16 | Wk 28 | Wk 40 |
| Artesunate |  | X | X | +/- |  |  |  |  |
| Informed consent | X |  |  |  |  |  |  |  |
| Demographics | X |  |  |  |  |  |  |  |
| Complete History | X |  |  |  |  |  |  |  |
| Physical exam | X |  |  |  |  |  |  |  |
| Vitals signs | X | X | X2 | X2 | X | X | X | X |
| Urine hCG (if female) | X | X | X3 | X3 |  |  |  |  |
| HIV test with reflex CD4 count | X |  |  |  |  |  |  |  |
| AE diary cards |  | X |  |  |  |  |  |  |
| Anal pap | X |  |  |  |  | X | X | X |
| Anal brushes | X | X | X2 | X2 | X | X | X | X |
| Anoscopy | X |  | X2 | X2 | X | X | X | X |
| HRA | X |  |  |  |  | X | X | X |
| HPV testing | X |  |  |  | X | X | X | X |
| Bloods for banking | X |  |  |  | X | X | X | X |

+/-: The patient may or may not get the Artesunate or undergo anal pap test depending on the dosing schedule they are assigned to.

***Please note that anoscopy is part of the HRA evaluation. Anoscopy without concurrent HRA will be used to evaluate for any toxicity to the local tissue at the dentate line at the week 6 visit.

****Participants who are on the 2 cycle dosing schedule will still be seen on cycle 3 week 4 but will not have a urine hCG test or get dispensed Artesunate.

1may be done as telemedicine visits

2will be obtained at in-person visits only

3for telemedicine dosing visits, the patient will do a home pregnancy test and will send a picture to the study team, along with an attestation of negative pregnancy test.

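### The one-cycle de-escalation levels in the protocol's diagrams conflict with the cycle range in section 5.1 and with the cycle 2 column of the study calendar, and must be reconciled

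*Protocol*

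**What the plan says.** **De-escalation diagrams (sections 5.1 and 14.1).** Besides cohorts I to VI, both show three further boxes, at 200, 400 and 600 mg. Each gives five daily doses per cycle and "1 cycle administered at week 0".

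**Section 14.1, text.** "The modification of the 3 + 3 design consists of the extra de-escalation steps as noted on the left of the diagram pictured below". Earlier in the section the same steps are introduced as follows: "there are possible intermediate dose de-escalation steps allowed (i.e. to have only one administration at a particular dose".

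**Section 5.1, text.** "the dosing schedules will vary between 2 and 3 cycles". The next paragraph describes six dose levels "with additional de-escalation steps".

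**Dose tables (synopsis, 5.1, 14.1).** Six rows each, all with 2 or 3 cycles.

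**Appendix A, study calendar.** The artesunate row has X at cycle 1, X at cycle 2 and +/- at cycle 3. The +/- symbol is explained so: "The patient may or may not get the Artesunate or undergo anal pap test depending on the dosing schedule they are assigned to". A further note covers participants on two cycles, who attend at week 4 without drug or pregnancy test. No note covers participants on one cycle.

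**Section 5.2.** The DLT period runs to one week after the last cycle. Two cases are worked out: "Thus, for the 2 cycles, the DLT determining period will extend to 3 weeks; for 3 cycles, it will extend to 5 weeks".

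**The concern.** The one-cycle levels are the feature that distinguishes this design from an ordinary 3 + 3. They come into play after DLTs have been seen, so the amount of drug given there should be beyond doubt. Instead, the treatment text leaves them outside its stated range, and the calendar, which sites use to plan visits, shows drug in cycle 2 for everyone.

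Two things are at stake. The first is safety: a patient assigned to a reduced schedule could receive the second cycle that the reduction removes. The second is the dose-finding decision: if some patients at a one-cycle level receive two cycles, their DLT outcomes do not belong to the level under which they are counted.

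**Working it through.** The two main conflicts are textual. Arithmetic helps with their size, and with whether the rest of the protocol recognises the one-cycle levels.

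**1. Side by side**

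| Place | One-cycle level? |
|---|---|
| Diagrams in 5.1 and 14.1 | Yes, at three doses |
| 14.1 text on the modification | Yes, by reference to the diagram |
| 14.1 text introducing the steps | Yes, but counted in administrations, not cycles |
| 5.1 sentence on schedules | No, 2 to 3 cycles |
| Dose tables (synopsis, 5.1, 14.1) | No row |
| Appendix A, artesunate row | No, cycle 2 unconditional |
| Appendix A, shorter-schedule note | No, two-cycle participants only |
| Synopsis and Dosage and Administration | Compatible: up to 3 cycles |
| Symptom diary (Appendix B) | Yes: 1, 2 or 3 planned cycles |
| 14.2, sample size | Compatible: extra patients for de-escalation in cycle frequency |

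**2. Exposure under the two schedules.** Doses per patient = 5 × number of cycles.
- Diagram: 5 × 1 = 5 suppositories.
- Calendar: X in cycles 1 and 2 gives 5 × 2 = 10 suppositories.
- Total drug: 1,000 against 2,000 mg at 200 mg; 2,000 against 4,000 mg at 400 mg; 3,000 against 6,000 mg at 600 mg.

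The ratio is 2 at each dose. With drug at weeks 0 and 2, the regimen is that of cohort I, III or V at the same dose.

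**3. DLT period.** Reproducing section 5.2 first: week of the last cycle + 1 gives 2 + 1 = 3 weeks for two cycles and 4 + 1 = 5 weeks for three, both as stated. The same rule for a single cycle at week 0 gives 0 + 1 = 1 week. Counting from the last dose instead (first dose on day 0, fifth on day 4) gives:
- one cycle: (0 + 4 + 7)/7 = 1.57 weeks;
- two cycles: (14 + 4 + 7)/7 = 3.57 weeks;
- three cycles: (28 + 4 + 7)/7 = 5.57 weeks.

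The last two do not match the stated values, so the protocol counts from the week in which the cycle starts. The general rule therefore yields a one-cycle period; it is only not written out. If a second cycle were given at the nominal week 2, its toxicity would fall after a period ending at week 1. Whether it counted would depend on which schedule the patient was taken to be on.

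**4. Sample size.** 6 levels × 6 = 36, the stated expected number. With three one-cycle levels and 6 more patients to bring the MTD cohort to 12: 9 × 6 + 6 = 60, the stated maximum. Without the one-cycle levels: 6 × 6 + 6 = 42, or 36 + 12 = 48 if all 12 expansion patients are new. The protocol does not itemise the 60, so this split is an inference, but it suggests that the one-cycle levels were planned for.

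**The case against.** The strongest reply is that the one-cycle levels are adequately specified and that this is untidy wording. The diagrams give dose, doses per cycle, number of cycles and week. The DLT rule applies to any number of cycles. The synopsis and dosing section allow up to 3 cycles, the diary offers a one-cycle option, and the sample size makes room for these levels. The sentence in 5.1 follows the six-cohort table and may describe only that table. Drug is dispensed one cycle at a time on an order, so the calendar is not the dispensing instruction.

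Most of this stands, and it rules out some stronger readings that a reader might infer:

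- *That a de-escalated cohort cannot be run, judged or declared the MTD, or that the DLT period contradicts it.* Not supported, for the reasons just given.
- *That section 14.1 prescribes a single suppository.* Strained. The table in that section uses administration in the heading of a column that lists the cycle weeks, and the text then points to the diagram with its five daily doses. The wording is loose and needs aligning, but it does not establish a third schedule.
- *That the chance of opening a one-cycle level can be calculated.* It would require knowing which cohort leads to which step. The arrows are not legible in the available text, and the wording says only that the steps are possible if DLTs occur. Such a figure would in any case measure how often a level is reached, not how often a dosing error follows.

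What the reply does not remove is the conflict with 5.1 and, above all, with the calendar. The conditional mark appears only in cycle 3, and the section on compliance with self-administration likewise schedules dosing visits at weeks 0, 2 and 4 without exception. The week 2 visit may be by telemedicine with drug shipped home, so an in-person check may not intervene. The evidence that one-cycle levels are intended makes the gaps elsewhere more worth closing.

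**Conclusion.** The point holds as an internal inconsistency that should be corrected. Section 5.1's cycle range and the cycle 2 column and notes of Appendix A do not accommodate the one-cycle levels that section 14.1 calls the modification of the design. The dose tables omit those levels, and section 14.1 describes them in a unit different from the diagram's.

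The size is a factor of two in exposure, 5 against 10 suppositories, for a patient on a one-cycle level who is dosed by the calendar. This assumes that the site follows the calendar row literally; the documents do not say how likely that is. If it happened, the level's DLT count would mix two regimens and could not be interpreted. The missing one-cycle value in section 5.2 is a minor clarification. No sample size or DLT threshold changes.

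**What to change.** The sponsor should confirm the intended schedule for the de-escalation levels, then make these places agree with each other and with the diagrams:

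- the sentence in section 5.1 on the range of cycles;
- the dose tables in the synopsis, 5.1 and 14.1, so that every level that may be opened is listed;
- the description of the step in section 14.1, in the same unit as the diagram;
- the cycle 2 column of Appendix A (artesunate and pregnancy test) and its notes, so that they state what applies to every schedule that remains in the protocol.

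As a minor addition, section 5.2 should write out the DLT period that its existing rule gives for any one-cycle level.

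Which schedule is right is for the protocol team to decide. The cost is amendment wording; these edits in themselves add no patients, visits or tests.

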**Cohort I**:

**200 mg** x 5 daily doses/cycle.

**2 cycles** administered at weeks 0, 2

**Cohort III**:

**400 mg** x 5 daily doses/cycle.

**2 cycles** administered at weeks 0, 2

**Cohort IV**:

**400 mg** x 5 daily doses/cycle.

**3 cycles** administered at weeks 0, 2, 4

**De-escalate** to **200 mg** x 5 daily doses/cycle.

**1 cycle** administered at week 0

**De-escalate** to **400 mg** x 5 daily doses/cycle.

**1 cycle** administered at week 0

**Cohort II**:

**200 mg** x 5 daily doses/cycle.

**3 cycles** administered at weeks 0, 2, 4

**Cohort VI**:

**600 mg** x 5 daily doses/cycle.

**3 cycles** administered at weeks 0, 2, 4

**Cohort V**:

**600 mg** x 5 daily doses/cycle.

**2 cycles** administered at weeks 0, 2

**De-escalate** to **600 mg** x 5 daily doses/cycle.

**1 cycle** administered at week 0

**At MTD, expansion cohort**, n = 12.

De-escalate

De-escalate

De-escalate

De-escalate

## Definition of Dose-Limiting Toxicity

A dose-limiting toxicity (DLT) is defined as any drug-related Grade 2 (moderate; minimal, local, or noninvasive intervention indicated; limiting age appropriate instrumental ADL) or greater drug-related toxicities in any organ system (or Grade 3 or greater toxicities–severe or medically significant but not immediately life-threatening; hospitalization or prolongation of hospitalization indicated; disabling; limiting self care ADL**) in any organ system (including gastrointestinal, dermatologic, and neurologic), as delineated in Common Terminology Criteria for Adverse Events v4.0 (CTCAE).

This above definition of dose-limiting toxicity applies to the drug that is being studied—the artesunate suppository. Post-procedural complications related to the HRA procedure are not dose limiting.

The dose limiting toxicity determining period for the study will extend to 1 week after the last cycle of artesunate suppository. Thus, for the 2 cycles, the DLT determining period will extend to 3 weeks; for 3 cycles, it will extend to 5 weeks.

Beyond the DLT determining period, if patients in a specific cohort have complete resolution of their high-grade dysplastic lesions, then the plan will be to stop at this dosing cycle and frequency and move into the 12-patient expansion cohort.

Management and dose modifications associated with the above adverse events are outlined in Section 6.

Dose escalation will proceed within each cohort according to the modified 3+ 3 design with de-escalation schema and an expansion cohort at MTD. Dose-limiting toxicity (DLT) is defined as above.

The specific details are as follows,

The 3 + 3 dose escalation will consist of 6 dose levels in combination with variation in dosing schedules the single agent Artesunate, with additional de-escalation steps. An expansion cohort of 12 patients will be included at the MTD. Once MTD is found, then secondary outcomes will be evaluated. In MTD expanded patient cohort, anal intraepithelial neoplasia (AIN) regression from AIN 2/3 to low-grade anal intraepithelial neoplasia (AIN 1) or no residual AIN will be assessed through subsequent HRA evaluation. Cytology specimens will be tested through quantitative PCR for HPV viral load during initial and subsequent HRA evaluations. A tissue bank will be created for future studies.

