| **Statistical Methods**:   1. **Definition of primary outcome/endpoint:** This is a Phase I modified 3 + 3 design, in which the MTD will be identified. 2. **Definition of secondary outcomes/endpoints:**  - Downgrade in AIN 2/3 to AIN 1 or no AIN - HPV genotype testing—optimally to undetectable levels of HPV at week 40 of follow. - Creating of tissue bank for future studies.   **Analytic plan for primary objective:** This is a Phase I modified 3 + 3 design, in which the MTD will be identified. Based on previous studies of rectally administered Artesunate for the treatment of malaria, the safety profile demonstrates a low probability of dose limiting toxicity in children, as well as adults. The initial dose will be a 200 mg suppository administered in cycles of 5 daily doses at weeks 0 and 2. Dose escalation will proceed with a 3 + 3 design with the safeguard of an integrated de-escalation schema. At the MTD, an expansion cohort of 12 patients will be included.  Note: Each cycle = 5 days   | **Dose Escalation Design** | | | | | | --- | --- | --- | --- | --- | | **Cohort** | **Dose (mg)** | **Number of Treatment Cycles** | **Designated Weeks of Artesunate Administration** | **Number of patients** | | **I** | 200 | 2 | 0, 2 | 3 | | **II** | 200 | 3 | 0, 2, 4 | 3 | | **III** | 400 | 2 | 0, 2 | 3 | | **IV** | 400 | 3 | 0, 2, 4 | 3 | | **V** | 600 | 2 | 0, 2 | 3 | | **VI** | 600 | 3 | 0, 2, 4 | 3 |   ***According to the standard of care clinical practice, a postoperative visit will be done 4 weeks after ablation, i.e. either on week 20 or on week 32   1. **Analytic plan for secondary objectives:**     1. For the dichotomous variables of regression of AIN 2/3, counts, percents and 95% confidence levels will be calculated.    2. HPV viral genotyping will be assessed to determine when HPV viral load will become undetectable.    3. Tissue bank of specimens for future studies. 2. **Sample size justification:** In this phase I dose escalation trial, 6 dose levels will be considered for a total sample size of 36-60 patients with a target dose limiting toxicity (DLT) of < 18%. |
| **Funding, Regulatory, and Feasibility Issues:**  Frantz Viral Therapeutics will supply the Artesunate suppositories at no cost. The suppository will be obtained from an off-site pharmacy (Buderer Drug Company).  Buderer Drug Company will ship suppositories to the Johns Hopkins Hospital Investigational Drug Pharmacy for each patient enrolled in the study. |

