## Analysis of Primary and Secondary Endpoints

- - 1. Analysis of safety endpoints

The NCI common terminology criteria for adverse events (AE) (CTCAE 4.0) will be used to evaluate toxicity. We will consider a toxicity to be an adverse event that is possibly, probably or definitely related to treatment. The maximum grade of toxicity for each category of interest will be recorded for each patient, and the summary results will be tabulated by category, grade, and dose level. Serious (≥ Grade 3) toxicities will be described on a patient-by-patient basis and will include any relevant baseline data.

Once the MTD (or RP2D) is found, then secondary outcomes will be evaluated based on MTD.

- - 1. Analysis of secondary efficacy endpoints

Regression of AIN 2/3 to either AIN 1 or the absence of AIN will be used as dichotomous variables and the proportion of patients with the characteristics and the corresponding 95% confidence intervals will be calculated.

HPV viral genotype will be collected longitudinally over time as a qualitative measure.

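### Section 5.2 stops escalation and opens the expansion on lesion resolution, while every other section escalates on DLTs and expands at the MTD, and no rule selects an RP2D

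*Protocol*

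**What the plan says.** Section 5.2 sets the DLT window at 3 weeks for two cycles and 5 weeks for three. For the time after that window it adds: "if patients in a specific cohort have complete resolution of their high-grade dysplastic lesions, then the plan will be to stop" at that dose and schedule and go to the 12-patient expansion. No other section repeats this rule. Later in 5.2 itself, the expansion and its regression assessment are tied to the MTD: "In MTD expanded patient cohort, anal intraepithelial neoplasia (AIN) regression from AIN 2/3".

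Section 14.1 decides escalation on DLT counts alone: "If none of the three patients in a cohort experiences a dose-limiting toxicity, another three patients will be treated at the next higher dose" level. It defines the MTD as the top tested level with at most 20% DLTs. It then says "An expansion cohort will occur at MTD" and that, once the MTD is known, "additional patients will be added to this cohort to allow a total of 12 patients". The synopsis agrees: "At the MTD, an expansion cohort of 12 patients will be included". Section 5.1 says the same.

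Section 14.1 gives the aim as "to determine the MTD or recommended Phase 2 dose (RP2D) of Artesunate", but neither it nor 14.3 says how an RP2D would be chosen. Section 14.3 reads: "Once the MTD (or RP2D) is found, then secondary outcomes will be evaluated based on MTD".

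**The concern.** Two rules in the current text can lead to different dose assignments. Take a cohort with no DLTs in three patients whose high-grade lesions later resolve. Under 14.1 the trial has moved up and keeps moving up until toxicity or the top level. Under 5.2 it stops at the resolved cohort's dose and expands there. That dose would then receive the patients that the rest of the protocol reserves for the MTD, and the synopsis endpoint, the maximum safe dose, might not be reached.

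The 5.2 trigger also cannot be applied as written. It does not say how many patients must resolve, at which visit, or what happens to accrual at higher levels already open. The visit matters because 8.3.8 sends residual disease at weeks 16 and 28 to surgical ablation, so later clearance may be the surgeon's result rather than the drug's. If the patients who fired the rule are also counted in the expansion, the regression proportion is selected upward.

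**Working it through.** **The plan's own figure.** Section 14.2 expects 36 patients from the 3+3 and allows up to 60. 6 levels × 6 = 36. One reading that gives the ceiling is 36 + 3 one-cycle de-escalation levels × 6 + 6 to take the MTD cohort from 6 to 12 = 60. The protocol does not spell this out, so it does not settle whether the 12 are all new patients.

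**Timing.** Inputs are 6 evaluable patients per month (14.2), about one per 0.72 week; DLT windows of 3 or 5 weeks (5.2); a one-week washout between levels (14.1), taken as 0 or 1 extra week; and first HRA/biopsy at week 16 (synopsis, 8.3.7). The first patient enters at time zero or after one interval. Results are in weeks from study start.

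| | 3 per level | 6 per level (3, one window, 3 more) |
|---|---|---|
| Cohort I week 16 results complete | 17.4–18.2 | 21.9–23.3 |
| Cohort II fully enrolled | 5.9–8.3 | 16.8–20.7 |
| Cohort III (400 mg) | fully enrolled 12.3–16.5 | opens 21.8–27.4 |

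Cohort II is full before cohort I's results in every scenario. The visit window of ±2 weeks at week 16 (8.2) does not change this: the smallest gap is 23.3 − 20.7 = 2.6 weeks. It could change the order for cohort III, where 18.2 − 2 = 16.2 falls before 16.5, so nothing here relies on cohort III being full.

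**Chance that the trigger fires in one 3-patient cohort.** With resolution rate r, all 3: r³; at least 2: 3r²(1−r) + r³; at least 1: 1 − (1−r)³. The document gives no rate for artesunate. 17% and 24% are the complete-response rates that 2.2 gives for 5-fluorouracil and imiquimod; 30% is an assumption.

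| r | all 3 | at least 2 | at least 1 |
|---|---|---|---|
| 17% | 0.5% | 7.7% | 42.8% |
| 24% | 1.4% | 14.5% | 56.1% |
| 30% | 2.7% | 21.6% | 65.7% |

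The undefined patient count alone moves the probability more than 20-fold. With 6 patients who must all resolve, it is 0.30⁶ = 0.07% even at 30%.

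**Bias if the trigger patients count within the 12.** The expected regression proportion is (E[trigger responders] + 9r)/12, taking resolution and regression to occur at the same rate.

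- Trigger 3 of 3: (3 + 9r)/12. At 17%: (3 + 1.53)/12 = 38%. At 24%: (3 + 2.16)/12 = 43%.
- Trigger at least 1 of 3: E = 3r/[1 − (1−r)³]. At 17%: 0.51/0.428 = 1.19, and (1.19 + 1.53)/12 = 23%. At 24%: 0.72/0.561 = 1.28, and (1.28 + 2.16)/12 = 29%.
- 12 new patients: no bias from this source.

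**The case against.** The strongest defence is that the rules act in sequence. The 14.1 decision follows the 3- or 5-week window; 5.2 applies only afterwards, and no biopsy exists before week 16. A reader might infer that both rules speak at one moment about the same cohort. They normally do not, and that part of the defence stands. But the sequence creates the practical problem: when 5.2 fires, a higher level is usually open, and nothing says whether its accrual stops.

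One could also argue that a level stopped under 5.2 is the top level tested, hence the MTD. That holds only if no higher level has been tested, and the timing makes this unlikely.

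A reader might infer that the primary objective would go unanswered. The documents do not support that. The stated objective is safety and tolerability, 14.3 tabulates toxicity by dose level wherever escalation ends, and 14.1 admits an RP2D as an alternative target. What may be missed is the synopsis endpoint of a maximum safe dose. Nor is 14.3 left with nothing to analyse: a proportion and interval can be computed for whichever cohort is expanded. The fault is that its wording ties the analysis to the MTD.

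On ablation, 8.3.8 read alone suggests that any residual disease at week 16 is ablated. The synopsis schema sends only patients without improvement to the operating room then, so an improving patient who is clear at week 28 may be unablated. Week 16 is therefore not the only defensible visit.

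Finally, 38% should not be taken as the expected bias. It belongs to the rarest trigger and requires trigger patients to count in the 12. The total of 12 in 14.1 suggests that they do; the synopsis and 5.1 can be read as 12 new patients.

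**Conclusion.** The inconsistency stands. One sentence in 5.2 stops and expands on activity; the synopsis, 5.1, 14.1 and the rest of 5.2 escalate on DLTs and expand at the MTD. Naming an RP2D does not reconcile them, because no rule selects one and 14.3 still evaluates on the MTD. At the planned accrual, the next level is fully enrolled before the first cohort's week 16 results are complete, so a dose fixed by 5.2 would usually be neither the highest level tested nor the MTD.

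How often this would occur cannot be stated, because the trigger is undefined and all resolution rates used are assumptions. If all patients must resolve, firing is rare; if one suffices, it is likely. The upward bias is conditional on firing, ranges from none to the 23–43% shown for assumed true rates of 17–24%, and concerns a descriptive secondary endpoint. This deserves correction because it governs dose assignment, but it does not undermine the safety reporting.

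**What to change.** Choose one of two repairs.

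1. Delete the sentence in 5.2, so that escalation and expansion follow 14.1 alone.
2. Move it to 14.1 as an explicit RP2D rule that states:
   - how many patients must resolve;
   - one visit, assessed before any ablation (week 16, or week 28 in unablated patients), using the protocol's regression assessment by HRA/biopsy and anal cytology;
   - whether accrual at higher open levels stops.

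Under the second option, report the dose as an RP2D selected on activity, not as the MTD, and change 14.3 so that secondary outcomes are evaluated at the MTD or the RP2D. State whether the trigger patients count within the 12; if they do, also show the regression proportion without them.

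The sponsor should set the patient count deliberately: requiring everyone to resolve comes close to deleting the rule. The cost is wording in 5.2, 14.1 and 14.3. The HRA, biopsy and cytology are already planned, so neither option needs extra visits or tests. Neither needs extra patients unless the sponsor chooses 12 new ones where the current plan would have filled the cohort to 12.
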